### Sample size

We conducted two separate power analyses for the RCT; one for the functional outcome and one for the cognitive outcome. The power calculation for the functional outcome is based on two previous studies [18,19]. These studies found large effects of CPAP treatment on functional outcome measures in stroke patients. To detect at least one standard deviation (large effect) on functional outcome with 90% power and an alpha of 0.05 (one-tailed), a minimum of 34 patients (17 per arm) is required.

No reliable information on the expected effect of CPAP treatment on cognitive measures is available. Therefore, an effect size of 0.75 standard deviation was used to estimate the necessary sample size. Taken the same alpha level and 80% power, a minimum of 56 patients (28 per arm) needs to be included in the RCT. The compliance in this study is expected to be relatively high (around 67%) due to the relatively short duration of the experimental treatment phase and the assistance of a specially trained staff. Taking the compliance rate into account, a total of 70 patients will be the target sample size for the RCT.

For the supplementary case–control study, we set the sample size at 70 OSA patients and 70 patients without OSA, which allows detection of a medium size effect (0.5 standard deviation) with 90% power, and p-value set at 0.5.

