### Statistical analyses

All statistical analyses will be performed with SPSS 19 (IBM; Armonck, USA) or later versions of this package. Depending on the level of measurement, parametric statistics (Student’s *t*-test and analysis of (co)variance) or non-parametric statistics (*χ*^2^ and Fisher’s exact test) will be used. Statistical significance will be set at a p-value of 0.05 or less. Socio-demographic and clinical characteristics at baseline will be presented using descriptive statistics. If group differences are observed at baseline on one or more background variables, those variables will be included as covariates in all further analyses.

For the RCT, the therapy effects on the primary and secondary outcome measures will be examined using a two factor (group × time) multivariate analysis of variance (MANOVA). Effect sizes will be calculated for all analyses using standard statistical procedures. To control for the multiple comparisons of cognition and functional status, two separate MANOVA’s will be performed. Given that we have two primary outcomes defined for the study (i.e., cognitive and functional outcomes), we will subsequently follow Hochberg’s step-up procedure [36] to control the false discovery rate.

Data will be analyzed according to the intention-to-treat principle. Additionally, a per-protocol analysis will be performed. Depending on the variability of compliance, a secondary analysis of good versus poor compliance will be conducted. In an exploratory analysis, we will investigate whether the effectiveness of CPAP therapy varies as a function of clinical diagnosis, level of cognitive functioning, and demographic background.

For the supplementary case–control part of the study, OSA patients will be compared with the control group of non-OSA patients on primary and secondary outcome measures using a MANOVA. As with the RCT, a separate analysis will be performed for cognition and functional status, and the Hochberg’s step-up procedure will be followed. For the follow-up of the USER-P questionnaire, within group changes will be assessed using paired t-tests and between group comparison will be made with two sample *t*-test.

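### The compliance allowance that raises the RCT from 56 to 70 patients does not preserve 80% power for cognition under the planned intention-to-treat analysis

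*Protocol article*

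**What the plan says.** Under Sample size, the functional calculation uses a one-tailed alpha of 0.05. The cognitive calculation assumes 0.75 SD, chosen because no reliable estimate existed, and continues: "Taken the same alpha level and 80% power, a minimum of 56 patients (28 per arm) needs to be included in the RCT". The article then expects compliance of around 67% and ends: "Taking the compliance rate into account, a total of 70 patients will be the target sample size for the RCT". It shows no formula for the step from 56 to 70.

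The abstract divides the 70 patients equally, 35 per arm. Under Statistical analyses the main analysis set is fixed: "Data will be analyzed according to the intention-to-treat principle". A per-protocol analysis is additional. The treatment effect is tested by a group × time MANOVA, run separately for cognition and for functional status. On the significance level the section says only: "Statistical significance will be set at a p-value of 0.05 or less". It does not state sidedness.

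**The concern.** An allowance for non-compliance can mean two different things. If non-compliers leave the analysis, enough extra patients must be recruited to replace them. If they stay in, as intention to treat requires, the average effect in the CPAP arm falls, and the required size grows with the square of that dilution. The article's allowance looks like the first kind, while its main analysis is of the second kind.

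Cognition is one of the two primary outcomes, and it is the calculation that sets the size of the trial. A reader will take 70 as the number that keeps 80% power once compliance is allowed for. If it does not, a null cognitive result would look better powered than it is. The article's own Background faults earlier null CPAP trials for low compliance and insufficient power.

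**Working it through.** **Inputs.** From Sample size: effect 0.75 SD, power 80%, 28 per arm, compliance 67%, target 70. From the abstract: 35 per arm. From Statistical analyses: intention to treat, significance level 0.05. Sidedness is unresolved, so both versions are shown.

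**1. Reproduce 56.** The normal approximation is n per arm = 2(z_α + z_β)²/d².
- Two-sided 0.05: 2(1.960 + 0.842)²/0.75² = 27.9, so 28 per arm. This matches 56. The t-test needs 29, and at 28 per arm its power is 78.7%.
- One-tailed 0.05, the level the text refers back to: 2(1.645 + 0.842)²/0.75² = 22.0, so 22 per arm (23 by t-test). This does not give 56.

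The stated 56 therefore fits a two-sided test, although the text names a one-tailed one.

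**2. Reproduce 70.**
- Replace non-compliers in both arms: 56/0.67 = 83.6, so 84.
- Replace them in the CPAP arm only: 28 + 28/0.67 = 69.8, so 70.

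Only the second gives 70 from the stated 67%. (56/0.80 is also 70, but that would be a 20% loss, which the text does not mention.)

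**3. What that size protects.** With 35 in the CPAP arm, 35 × 0.67 = 23.45 comply. Comparing 23 or 24 compliers with 35 controls at 0.75 SD gives 78% or 79% power (t-test, two-sided), about the same as 28 v 28. The allowance thus fits the per-protocol comparison.

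**4. Intention-to-treat power at 35 per arm.** Assume that 0.75 SD is the effect in compliers, that 67% is the share of patients who comply, and that non-compliers keep a fraction f of the effect. The average effect is then 0.75 × (0.67 + 0.33f). Power is from the noncentral t with 68 degrees of freedom and noncentrality d√(35/2).

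| f | Average effect (SD) | Two-sided 0.05 | One-tailed 0.05 |
|---|---|---|---|
| 0 | 0.50 | 54% | 67% |
| 0.25 | 0.56 | 64% | 76% |
| 0.50 | 0.63 | 73% | 83% |
| 0.75 | 0.69 | 81% | 89% |
| 1 (no dilution) | 0.75 | 87% | 93% |

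**5. Detectable effect and break-even.** At 35 per arm, 80% power needs an average effect of 0.68 SD two-sided or 0.60 SD one-tailed. Setting 0.75 × (0.67 + 0.33f) equal to these gives f of about 0.7 two-sided and 0.4 one-tailed. With f = 0, 80% power would need 64 per arm two-sided or 50 one-tailed.

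**6. The planned test.** For one outcome at two visits, group × time is a comparison of change scores, with standardised effect d/√(2(1 − ρ)), where ρ is the correlation between visits. At f = 0 (d = 0.5025):
- ρ = 0.4: 47% two-sided, 60% one-tailed
- ρ = 0.5: 54% and 67%, as in step 4
- ρ = 0.6: 64% and 75%
- ρ = 0.7: 76% and 85%

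These correlations are assumptions, since the article gives none. The actual MANOVA covers nine domains and three visits, and its power cannot be derived from what is stated.

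**The case against.** A reader might infer more than the article supports, in three ways.

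- **That the planned analysis has 54% power.** It does not follow. That figure belongs to a two-sample t-test, two-sided, with no benefit at all in non-compliers. The planned test uses baseline, and its power may be higher or lower depending on the correlation. Compliance may also be graded: the device records use per night, and Statistical analyses refers to variability of compliance and to good versus poor compliance. On the one-tailed level that the text names, the shortfall is gone once non-compliers keep about 40% of the effect. This objection stands, and it is why a range is given.
- **That 70 is an arithmetic slip for 84.** The figure can be reproduced, and the planned per-protocol comparison has roughly the intended power. The fault is a mismatch between the allowance and the main analysis set.
- **That the 80% is stated for 70 patients under intention to treat.** The article attaches it to 56 patients. That 70 carries it over is implied by the wording of the allowance.

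It can also be argued that 0.75 SD is already the average effect over all randomised patients, which would give 87% power two-sided and 93% one-tailed. But then no compliance allowance would be needed, and the article makes one. Finally, the Discussion admits a relatively small sample. That softens the risk of misreading, but it gives no power and does not correct the calculation.

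**Conclusion.** The point holds as a mismatch between the compliance allowance and the main analysis. The increase to 70 treats non-compliers as replaceable, while intention to treat averages over them. At 35 per arm, power for cognition runs from about 54% to 81% two-sided, or 67% to 89% one-tailed, as non-compliers keep from none to three quarters of the effect. It reaches 80% only if they keep about 70% (two-sided) or 40% (one-tailed), and nothing in the article supports either share.

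This rests on three readings that the article does not spell out: 0.75 SD is the effect in compliers, 67% is a proportion of patients, and a two-sample comparison stands in for the MANOVA. No single power figure is justified. Nor do the documents support making a different primary analysis, such as ANCOVA, part of the correction, because any gain would depend on a correlation they do not report.

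**What to change.** Keep 70 patients and the planned analysis. In Sample size:

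- State what the allowance assumes: that 0.75 SD is the effect in compliers, that 67% is the share of patients who comply, and what benefit non-compliers are taken to have.
- Replace the implied 80% for cognition with the intention-to-treat power at 35 per arm as the range in the working, described as that of a two-sample comparison, and note that the MANOVA's power also depends on the correlation between visits.
- Name the sidedness used, and reconcile the one-tailed wording with the figure of 56, which fits a two-sided test.
- State the intention-to-treat effect detectable at 80% power with 35 per arm: 0.68 SD two-sided or 0.60 SD one-tailed.

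Suggested wording: *With 35 patients per arm, 67% of patients compliant and an effect of 0.75 SD in compliers, a two-sample intention-to-treat comparison of cognition has about 54% to 81% power (two-sided 0.05; 67% to 89% one-tailed) if non-compliers retain 0% to 75% of the effect.*

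This changes text only, with no extra patients or assessments. The cost is that a stated figure becomes less favourable.

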The TOROS project consists of a randomized controlled trial (RCT), and a supplementary case–control study. The primary objective of the RCT is to evaluate whether CPAP treatment improves cognitive and functional outcomes in stroke patients with OSA (AHI ≥ 15), as assessed by a neuropsychological test battery and by measures of neurological status and functional dependence. The aim of the supplementary case–control study is to explore the association between OSA and cognitive and functional status in stroke patients. Our hypothesis is that stroke patients with OSA have a poorer functional status and greater cognitive impairment compared to stroke patients without OSA. In both the RCT and the case–control study the secondary objectives are: 1) to evaluate the effects of OSA (and its treatment) on sleep quality, fatigue and mood; and 2) to evaluate the long-term effects of OSA on societal participation.

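### The case-control sample-size sentence gives a significance level of 0.5, and at 0.05 its 90% power holds only for a one-tailed test that it does not state

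*Protocol article*

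**What the plan says.** The Sample size section of the protocol article justifies 70 OSA and 70 non-OSA patients for the case-control study with the statement "which allows detection of a medium size effect (0.5 standard deviation) with 90% power, and p-value set at 0.5". It does not say whether the test is one- or two-tailed.

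The Statistical analyses section says "Statistical significance will be set at a p-value of 0.05 or less", again without sidedness, in the paragraph that governs all analyses. For the case-control part it plans that "OSA patients will be compared with the control group of non-OSA patients on primary and secondary outcome measures using a MANOVA", with separate analyses for cognition and functional status and Hochberg's procedure across the two.

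Two other places bear on sidedness. The Background states a directional hypothesis for this part: "stroke patients with OSA have a poorer functional status and greater cognitive impairment" than those without OSA. The only mention of one-tailed testing is in the RCT calculation for the functional outcome; the RCT cognitive calculation refers back to the same alpha level.

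**The concern.** The printed level and the analysis threshold differ by a factor of ten, so both cannot stand. The level is also one of the inputs from which the 90% should follow, and it does not follow.

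Correcting the level alone leaves a second gap. At 0.05 the stated power depends on a one-tailed test, whereas the F test of a MANOVA has no direction. A reader who corrects the misprint and keeps the planned analysis would credit the comparison with more power than a two-sided test of one outcome has. What is at stake is the accuracy of the power claim for one of the two parts of the project, not the way its results will be judged.

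**Working it through.** **Inputs.** From Sample size: n = 70 per group, difference d = 0.5 SD, power 90%, level 0.5. From Statistical analyses: level 0.05, MANOVA. The power statement is treated as a two-sample t-test on one outcome, the simplest reading of an effect given in SD units.

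**Formulas.** Noncentrality: δ = d × √(n/2) = 0.5 × √35 = 2.958, with 138 degrees of freedom. Normal approximation to power: Φ(δ − z), where z is the critical value (the far tail is negligible at 0.05 and small at 0.5). Per-group size for 90%: n = 2 × (z + 1.282)² / d². The exact figures use the noncentral t distribution.

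**Step 1: the sentence as printed (level 0.5).**
- Two-sided: z = 0.674, Φ(2.284) = 98.9%; exact 98.9%. For 90%, n = 8 × (0.674 + 1.282)² = 30.6, so 31 per group.
- One-sided: z = 0, Φ(2.958) = 99.9%. For 90%, n = 8 × 1.282² = 13.1, so 14 per group.

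The stated 90% is not reproduced either way.

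**Step 2: level corrected to 0.05.**

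| Test | z | Power, normal | Power, t | n per group for 90% (normal / t) |
|---|---|---|---|---|
| One-tailed | 1.645 | Φ(1.313) = 90.5% | 90.3% | 69 / 70 |
| Two-sided | 1.960 | Φ(0.998) = 84.1% | 83.6% | 85 / 86 |

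The one-tailed t-test needs 69.2 per group, which rounds up to exactly the planned 70. This is the main reason to read 0.5 as a misprint for 0.05 and the basis as one-tailed.

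**Step 3: effect detectable with 90% power, two-sided 0.05, 70 per group.** (1.960 + 1.282) × √(2/70) = 0.548 SD by the normal approximation and 0.552 SD by t, so about 0.55 SD.

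**Step 4: can sidedness be inferred from the rest of the section?** The two RCT calculations, by normal approximation:
- Functional outcome, 1 SD, 90% power, 17 per arm stated. One-tailed: 2 × (1.645 + 1.282)² = 17.1. Two-sided: 2 × (1.960 + 1.282)² = 21.0. The stated number is near the one-tailed answer.
- Cognitive outcome, 0.75 SD, 80% power, 28 per arm stated. One-tailed: 2 × (1.645 + 0.842)² / 0.5625 = 22.0. Two-sided: 2 × (1.960 + 0.842)² / 0.5625 = 27.9. The stated number is near the two-sided answer.

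The section is not uniform, so the convention behind the case-control sentence cannot be read off its neighbours.

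**The case against.** The strongest reply is that this is a dropped zero and nothing more. The analysis section sets 0.05 for every analysis, so nobody following it would test at 0.5. The hypothesis is directional, the only sidedness named in the article is one-tailed, and 70 per group is the one-tailed t-test answer. On that reading both the 90% and the sample size are right.

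Most of this stands. The 0.5 is very likely a misprint, and the number of patients is not shown to be wrong. What does not follow is that the sentence then fits the plan. A directional hypothesis does not make a MANOVA F test one-tailed, and the sentence does not name the convention it needs.

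A reader might be tempted to go further in three ways that the documents do not support:
- *The risk of missing a 0.5 SD deficit is 16%, not 10%.* This assumes two-sided testing (100 − 83.6 = 16.4%), and the documents never say two-sided.
- *The MANOVA on nine cognitive domains has only 47% power.* That figure (Hotelling's test, squared multivariate distance D² = 0.25) describes one affected domain uncorrelated with the rest. If all nine domains shift by 0.5 SD with common correlation r, then D² = 9 × 0.25 / (1 + 8r), and power is about 77% at r = 0.5, 93% at r = 0.3 and over 99% at r = 0. For two functional scores both shifted by 0.5 SD, it runs from about 87% (r = 0.5) to 97% (r = 0). These patterns and correlations are assumptions; the article gives none, so no single multivariate figure should be quoted.
- *Hochberg's procedure lowers power to 75.5%.* That is the two-sided power at 0.025, a step reached only when the larger of the two p-values exceeds 0.05. If both are at or below 0.05, both hypotheses are rejected.

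**Conclusion.** The point holds in two parts. First, the significance level in the case-control sentence is wrong as printed: it conflicts with the analysis section and yields 98.9% power two-sided, not 90%. Second, once the level is read as 0.05, 90% power for 0.5 SD requires an unstated one-tailed test (90.3%). A non-directional comparison of a single outcome has 83.6%, and reaches 90% at about 0.55 SD. These figures assume equal groups of 70 with complete data and a t-test on one outcome.

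A reader might also infer that the decision rule for the case-control study is wrong. It is not: the 0.05 under Statistical analyses is the operative threshold, and the 0.5 appears only in the power sentence. The severity is minor to moderate, since this is a supplementary, exploratory part and the RCT calculation is untouched.

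**What to change.** In the case-control sentence, replace 0.5 with 0.05, state the sidedness, and make the power agree with the analysis. Either of two versions would do:
- **MANOVA kept:** with 70 per group and two-sided alpha 0.05, state about 84% power for 0.5 SD, or 90% power for 0.55 SD, and say that this refers to a single two-group comparison.
- **One-tailed testing intended:** keep 90% for 0.5 SD, write one-tailed alpha 0.05, and specify a directional test for the case-control comparison under Statistical analyses.

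The first version changes one sentence, and the stated power drops from 90% to about 84%. The second also changes the analysis description. Neither needs more patients. Keeping both 90% and 0.5 SD with two-sided testing would need 86 per group, which this point does not call for.

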### Statistical analyses

All statistical analyses will be performed with SPSS 19 (IBM; Armonck, USA) or later versions of this package. Depending on the level of measurement, parametric statistics (Student’s *t*-test and analysis of (co)variance) or non-parametric statistics (*χ*^2^ and Fisher’s exact test) will be used. Statistical significance will be set at a p-value of 0.05 or less. Socio-demographic and clinical characteristics at baseline will be presented using descriptive statistics. If group differences are observed at baseline on one or more background variables, those variables will be included as covariates in all further analyses.

For the RCT, the therapy effects on the primary and secondary outcome measures will be examined using a two factor (group × time) multivariate analysis of variance (MANOVA). Effect sizes will be calculated for all analyses using standard statistical procedures. To control for the multiple comparisons of cognition and functional status, two separate MANOVA’s will be performed. Given that we have two primary outcomes defined for the study (i.e., cognitive and functional outcomes), we will subsequently follow Hochberg’s step-up procedure [36] to control the false discovery rate.

Data will be analyzed according to the intention-to-treat principle. Additionally, a per-protocol analysis will be performed. Depending on the variability of compliance, a secondary analysis of good versus poor compliance will be conducted. In an exploratory analysis, we will investigate whether the effectiveness of CPAP therapy varies as a function of clinical diagnosis, level of cognitive functioning, and demographic background.

For the supplementary case–control part of the study, OSA patients will be compared with the control group of non-OSA patients on primary and secondary outcome measures using a MANOVA. As with the RCT, a separate analysis will be performed for cognition and functional status, and the Hochberg’s step-up procedure will be followed. For the follow-up of the USER-P questionnaire, within group changes will be assessed using paired t-tests and between group comparison will be made with two sample *t*-test.

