**Methods/Design:**

A randomized controlled trial will be conducted on the neurorehabilitation unit of Heliomare, a rehabilitation center in the Netherlands. Seventy stroke patients with obstructive sleep apnea will be randomly allocated to an intervention or control group (n = 2×35). The intervention will consist of four weeks of continuous positive airway pressure treatment. Patients allocated to the control group will receive four weeks of treatment as usual. Outcomes will be assessed at baseline, immediately after the intervention and at two-month follow-up.

In a supplementary study, these 70 patients with obstructive sleep apnea will be compared to 70 stroke patients without obstructive sleep apnea with respect to cognitive and functional status at rehabilitation admission. Additionally, the societal participation of both groups will be assessed at six months and one year after inclusion.

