
### Randomization and blinding

Participants with OSA will be randomized immediately after the baseline assessments. The minimization technique [25] will be used to minimize imbalance between the treatment arms for age, severity of OSA, stroke subtype (ischemic or hemorrhage) and severity of cognitive impairment. Assessors of cognitive and functional outcome measures will be blinded to treatment allocation.

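### The RCT's covariates are chosen by observed baseline differences, so the primary model depends on the data and the four minimization factors will almost never enter it

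*Protocol article*

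**What the plan says.** The Statistical analyses section gives a single rule for covariates: "If group differences are observed at baseline on one or more background variables, those variables will be included as covariates in all further analyses". It does not say what counts as an observed difference. The pool of candidates is open: the Secondary outcomes section introduces the socio-demographic and clinical characteristics by example (age, sex, education, BMI, medication use, life style variables), not as a closed list.

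The Randomization and blinding section says that minimization will "minimize imbalance between the treatment arms for age, severity of OSA, stroke subtype (ischemic or hemorrhage) and severity of cognitive impairment".

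For the RCT, therapy effects on primary and secondary outcomes "will be examined using a two factor (group × time) multivariate analysis of variance (MANOVA)". No fixed covariate is named for this model. Analysis of (co)variance appears only in a general sentence on methods. The RCT has 70 patients, "randomly allocated to an intervention or control group (n = 2×35)", and "Statistical significance will be set at a p-value of 0.05 or less".

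**The concern.** The two provisions pull against each other. Minimization is there to make the arms alike on four factors judged important enough to control at allocation. The covariate rule lets a variable in only when the arms are unlike on it. The better minimization works, the more surely its factors stay out of the analysis.

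Two consequences follow for the RCT. First, when allocation has balanced prognostic factors and the analysis ignores them, the standard error still counts the variance that those factors explain, although balancing has removed it from the treatment comparison. The standard error is too large, the test is conservative and power is lost. Second, which covariates enter the primary model is known only after the baseline data are seen. In a randomized comparison, differences on the remaining variables are chance, so the choice is unrelated to prognostic strength. Because the chosen set carries into all further analyses, it affects both primary outcomes.

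**Working it through.** **Inputs.** N = 70, 35 per arm (Abstract). Significance level 0.05 (Statistical analyses). Planned cognitive effect 0.75 SD (Sample size). Four minimization factors (Randomization and blinding). The share R² of variance in the analysed outcome explained by those factors is not given; I assume 0.1 to 0.3 and show 0.5 as an extreme.

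**The plan's own figure.** For 0.75 SD and 80% power, n per arm = 2(1.960 + 0.842)²/0.75² = 27.9, so 28 per arm and 56 in total. This is the stated figure, at a two-sided 0.05. (One-sided, it would be 2(1.645 + 0.842)²/0.75² = 22.0.) I therefore use two-sided 0.05 below.

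**Does the rule ever admit the factors?** I simulated 4,000 trials of 70 patients per scenario, with four two-level minimization factors and the preferred arm assigned with probability 1.0 or 0.8. There was one continuous outcome and six other background variables with no prognostic value. Because the protocol gives no threshold, I took an observed difference to mean baseline p < 0.05.
- At least one minimization factor admitted: 0% of trials (probability 1.0) or 0.2-0.4% (probability 0.8). Under simple 35:35 randomization it was 17%.
- At least one irrelevant variable admitted: 26-27% of trials, which agrees with 1 − 0.95⁶ = 26.5%.

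**Effect on the test, by formula.** With perfect balance and total within-arm SD 1, the unadjusted standard error is √(2/35) = 0.239, while the true one is 0.239 × √(1 − R²).
- Type I error without the factors = 2[1 − Φ(1.96/√(1 − R²))]. At R² = 0 it is 5.0%; at 0.1, 2[1 − Φ(2.066)] = 3.9%; at 0.3, 2[1 − Φ(2.343)] = 1.9%.
- Power at 0.75 SD without the factors = Φ[(0.75/0.239 − 1.96)/√(1 − R²)]. At R² = 0.1 it is Φ(1.241) = 89%; at 0.3, Φ(1.407) = 92%.
- Power with the factors = Φ[0.75/(0.239√(1 − R²)) − 1.96]. At R² = 0.1 it is Φ(1.347) = 91%; at 0.3, Φ(1.790) = 96%.

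**Effect on the test, by simulation.** This uses t-tests, imperfect balance and the rule itself, including the irrelevant covariates that it lets in. Ranges span the two assignment probabilities.

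| R² | Type I, protocol rule | Type I, factors fixed | Power at 0.75 SD, protocol rule | Power at 0.75 SD, factors fixed |
|---|---|---|---|---|
| 0.1 | 3.9-4.3% | 4.5-4.7% | 87% | 90% |
| 0.3 | 2.3-2.4% | 4.8-5.2% | 89-90% | 96% |
| 0.5 | 0.9-1.4% | 4.5-5.3% | 92% | 99% |

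The simulated powers under the rule lie two or three points below the formula, which uses z in place of t and ignores the irrelevant covariates.

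**What R² means here.** The group × time test is about change. A factor that shifts every assessment equally cancels out of it, so the relevant R² is the share of variance in change. If that is zero, type I error returns to 5% and nothing is lost.

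**The case against.** The strongest reply is that the harm is small and falls on the safe side. At the RCT's own planning effect, power stays at 87% or more under the rule, and the error is towards too few false positives. Age and stroke subtype may predict level far better than change, and baseline cognition is already in the model as a time level, so the relevant R² may lie at or below the bottom of the assumed range. All of that stands, and it limits the size of the point. It does not defend the rule, which still leaves the primary model open until the baseline data are seen.

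A reader might infer more than the documents support:
- *That the rule inflates false positives.* Omitting balanced factors makes the test conservative.
- *That the trial is left badly underpowered, judged at 0.5 SD.* In the Sample size section, 0.5 SD belongs to the case-control study. The RCT is planned on 0.75 SD (cognition) and 1.0 SD (function). One can reach 0.5 SD by diluting 0.75 by the expected 67% compliance (0.75 × 0.67 = 0.50). That assumes non-compliers gain nothing, which the protocol does not say, and the protocol cites compliance as its reason for enrolling 70 rather than 56.
- *That baseline significance tests are planned, with a calculable chance of a spurious difference.* The text speaks of descriptive statistics and observed differences. It states no test, threshold or number of variables, so the 26-27% above illustrates one reading and does not describe the plan.
- *That the factors are expressly excluded.* They are not. Age, for example, could still enter if imbalance remained within its minimization categories.

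The rule sits in the general paragraph and so also covers the case-control study. There, group differences can be real confounding and the minimization argument does not apply.

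**Conclusion.** The point holds for the RCT as a modest analysis fault that is easily mended. The protocol states the rule outright, so this is not a detail left to a fuller document. Followed as written, it leaves the primary model dependent on the data and almost always omits the four factors used for allocation.

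If those factors explain 10-30% of the variance of the analysed outcome, type I error is about 2-4% instead of 5%. Power at 0.75 SD with 35 per arm is about 87-90% instead of 90-96%, a loss of roughly 2 to 7 points. These sizes rest on the assumed R², on a single continuous endpoint in a linear model rather than the full MANOVA, and on all 70 patients being analysed. The loss shrinks towards nothing if the factors predict level but not change. That the covariate set is not fixed in advance does not depend on R².

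**What to change.** For the RCT, replace the rule with:

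> All RCT analyses include age, baseline AHI, stroke subtype and baseline severity of cognitive impairment as fixed covariates, whatever the observed baseline differences; no other covariates are added on the basis of observed differences.

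For the cognitive analysis, add a sentence stating how the cognitive-severity factor enters, because baseline cognition is already a time level in the group × time model and the two overlap. Limit the new wording to the RCT; it does not settle adjustment in the case-control study.

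The cost is about four of the 68 error degrees of freedom (70 − 2) in a two-arm comparison, and slightly more analysis work. The planned sample size does not change, and the four variables must be known before allocation in any case, because minimization uses them.
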